## Methods/design

### Aims of the trial

This study aims to compare the effectiveness of a web-based self-help intervention alone or combined with chat counseling in the reduction of the cannabis use of problematic cannabis users via a three-arm randomized controlled trial. The primary outcome is the weekly quantity of cannabis consumed (measured in the number of standard joints per week) at the 3-month follow up. The secondary outcome measures include the frequency of cannabis use days (7 day point prevalence of cannabis use days), changes in problematic cannabis use, severity of cannabis dependence, cannabis withdrawal symptoms, cannabis craving, the use of other psychoactive substances, mental health symptoms, functional health states, intervention satisfaction, and treatment retention. The predictive validity of participant characteristics for treatment retention and primary and secondary outcomes will be explored.

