### Measurement instruments

The primary outcome measures of cannabis consumption will be recorded as the 7-day point prevalence of the quantity of cannabis used, quantified in pre-defined standard cannabis joint sizes, as specified in the consumption diary (see also Table 
1). In the first step, participants will choose between three different cannabis forms presented in photographs (low potency cannabis plant, high potency cannabis plant, or cannabis resin). In the second step, five different standard joints for every category will be presented (1/10 g, 1/6 g, 1/4 g, 1/3 g, 1/2 g; pictures will come from the global drug survey cannabis meter
[32]); these joints will either be pure cannabis or cannabis mixed with tobacco. A standard tobacco cigarette, a ruler with centimeter and millimeter scales, the fraction amount in grams, and an open 10 cm paper prepared to roll a joint and containing the cannabis plant/resin-tobacco mixture or pure cannabis will be presented. Participants will choose which picture most closely approximates the cannabis joints they most often smoke. Those who smoke cannabis in different preparations (e.g., in a bong, a vaporizer, etc.) will choose the photograph that most closely approximates the amount of cannabis their usually consume. The final chosen picture will be placed in the individual consumption diary, and participants will be asked to convert the quantities of the cannabis they smoke into units relative to that picture if they consume cannabis for once in forms other than their common standard joint (rule of thumb that one high potency joint is equal to two low potency cannabis joints of identical content weight, one cannabis resin joint is equal to three low potency joints of identical content weight, etc.; identical content weight pictures will be presented on a separate page). Participants will also have the opportunity to indicate quantities below one common standard joint down to one tenth of a joint (they will also be able to indicate quarter-joint). Quantities smaller than one joint are expected for those who share cannabis joints with others.

**Table 1 T1:** Measurements and instruments

**Assessments/instruments**	**Baseline**	**1 week**	**3 weeks**	**6 weeks**	**3-month follow up**
Socio-demographics	x				
MHI-5	x				x
CLAMES^1)^	x				x
Quantity of Cannabis use^2)^	x	x	x	x	x
Frequency of Cannabis use^2)^	x	x	x	x	x
CUDIT	x				x
SDS	x			x	x
CWS		x	x		
CCS-7		x	x		
FDA	x			x	x
Intervention Satisfaction				x	

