Some participants may want to reduce their cannabis use only marginally and might reach their aims in the first weeks of the intervention, which might result in discontinuation of participation in the online self-help intervention. Therefore, we will recommend that participants reduce their cannabis by at least 20 to 30 percent in the first week of the intervention and continue with this strategy in subsequent weeks if they succeed. For participants who do not succeed, we will recommend that they create more modest goals until their final aim is received. Participants receiving chat counseling will additionally be motivated by their counselors to avoid setting their goals too low.

During the online implementation of the consumption diary of the web-based self-help intervention, pilot participants stressed the importance of the definition of common standard joints as the most appropriate measure for the consumption diary. On the one hand, the established cannabis meter pictures from the global drug survey website facilitated the pilot participants’ entry of their cannabis use, and, on the other hand, they felt more motivated by a tailored photograph than a written instruction. In our opinion, this is the most effective method to collect appropriate quantity measures, especially from cannabis users who use cannabis several times a day. However, as this is the first time this kind of quantity measure will be used in a randomized controlled trial, we will also rely on the number of days per week that cannabis is used.

One specific problem involves the online implementation of informed consent. As in previous research
[21], we will rely on participants to click on a field on the informed consent page and submit the consent with a submission button. Thus, we must trust that the participants have read and understood the study information and that they are at least 18 years old. However, as we followed the recommendations of
[47] and
[48] regarding the best implantation of online informed consent procedures, we expect that the participants will read the study information in full and provide informed consent.

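### The primary outcome is counted in one self-chosen joint unit, but the article gives no rule for a lasting change in usual joint size or potency

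*Protocol article*

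**What the plan says.** Under Aims of the trial, the primary outcome is the weekly quantity of cannabis at the 3-month follow up, "measured in the number of standard joints per week". The Hypotheses section frames the main comparison as the reduction in quantity from baseline to 3 months. A footnote to Table 1 takes the count from the last 7 days of the consumption diary.

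The unit is personal. Under Measurement instruments, a participant first picks one of three forms (low-potency plant, high-potency plant, resin) and then one of five sizes, "1/10 g, 1/6 g, 1/4 g, 1/3 g, 1/2 g". "Participants will choose which picture most closely approximates the cannabis joints they most often smoke". "The final chosen picture will be placed in the individual consumption diary".

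The instruction on conversion into that unit reads "convert the quantities of the cannabis they smoke into units relative to that picture if they consume cannabis for once in forms other than" the usual joint. The accompanying rule of thumb equates forms in the ratio 1:2:3 (low-potency plant, high-potency plant, resin) for joints of equal weight, and "identical content weight pictures will be presented on a separate page". Entries can go down to a tenth of a joint, and quarter-joints are possible. The reason given for such fractions is sharing.

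In the Discussion, "we will recommend that participants reduce their cannabis by at least 20 to 30 percent in the first week of the intervention".

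**The concern.** A count of joints measures quantity only while the joint stays the same. The written trigger for conversion is an exceptional use of another form. A participant who starts rolling smaller joints for good, or changes potency for good, has a new usual joint and not an exception, so the instruction as worded does not clearly reach that case. The aids compare potency at equal weight, so they do not help with a change in weight.

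Rolling smaller or weaker joints is one natural way to follow advice to cut by a percentage, and a target set as a number of joints can be met with fewer but larger ones. The first would be under-recorded and the second over-recorded, both in the primary outcome. If form and size are not collected at 3 months, no later analysis can recover them.

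**Working it through.** The article states no figure for this point, so there is none to reproduce. The sample size calculation does not depend on it.

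**1. Both readings of the diary rule.**
- If the picture stays in place, a lasting change falls outside the one-off wording, and the count may continue in a joint that is no longer the pictured one.
- If the picture may be chosen again, the unit itself changes between baseline and 3 months. The outcome is still described as a number of joints, with no weighting by grams or potency.

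Neither reading comes with a stated rule that keeps the two time points comparable.

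**2. Hidden change in weight.** Inputs: the five weights under Measurement instruments. With the same number of joints and no conversion, the recorded change is 0% and the true change is 1 − (new weight / old weight):
- 1/2 to 1/3 g: 1 − 0.667 = 33%
- 1/3 to 1/4 g: 1 − 0.75 = 25%
- 1/4 to 1/6 g: 1 − 0.667 = 33%
- 1/6 to 1/10 g: 1 − 0.60 = 40%
- Whole scale, 1/2 to 1/10 g: 1 − 0.20 = 80%

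Three of the four single steps exceed the recommended first-week cut of 20% to 30%. The fourth, 25%, lies inside it.

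**3. Hidden change in potency.** Inputs: the article's 1:2:3 rule at equal weight.
- High- to low-potency plant: 1 − 1/2 = 50%
- Resin to high-potency plant: 1 − 2/3 = 33%
- Resin to low-potency plant: 1 − 1/3 = 67%

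**4. The opposite error.** 14 joints × 1/6 g = 2.33 g, and 7 joints × 1/3 g = 2.33 g. The quantity is unchanged, but the unconverted count falls by 50%.

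**5. Illustration at arm level.** The share of participants who change is not in the document, so this rests on assumptions: 10% to 30% of an arm moves one step down, none of them converts, their number of joints is unchanged, and they consume the average amount.
- Low end: 10% × 25% = 2.5 percentage points of the arm's mean reduction missed
- High end: 30% × 40% = 12 percentage points missed

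The effect on the difference between arms cannot be computed, because it needs the share and direction of change in each arm.

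**6. Other measures.** Days of use per week do not reflect joint size or potency. The substance history questionnaire (FDA) is repeated at 6 weeks and 3 months and covers past-month use and the manner of use. It is not described as recording joint weight or potency, and it does not feed the primary outcome.

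**The case against.** A reader might infer that the picture is chosen once and locked, and that a lasting change is never captured. The text does not support that. It does not exclude re-selection. The one-off phrase may be loose English for exceptional use, and the core instruction is simply to express quantity in units of the picture. The grams are shown with the pictures and fractional entries are allowed, so a participant who chose 1/2 g and now rolls 1/4 g could enter 0.5 per joint. A hidden change of 25% to 50% is thus the result when nobody converts, not the expected result. Details of how the diary works may also sit in the full protocol.

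A reader might also infer a bias that differs by arm. This is plausible: the step-down advice, the joint-count goals in chat counseling and the harm-reduction material favoring oral intake all belong to the intervention, and the waiting list gets the program only after 3 months. But no rate of change is given for any arm, and the two errors act in opposite directions. Arm-dependent bias is a possibility, not a finding.

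The authors acknowledge that the measure is new to randomized trials and add days of use as a second measure. That mitigates little here.

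What stands after these objections is that the article writes a conversion rule for the primary outcome, limits it to one-off use, supports it only with equal-weight aids, and states nothing for a lasting change.

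**Conclusion.** The point holds as a gap in how the primary outcome is defined: the change in quantity from baseline to 3 months may miss real reduction or record reduction that did not occur. If unconverted, one step on the weight scale is worth 25% to 40%, and high- to low-potency plant is worth 50%. The figure of 2.5 to 12 percentage points for an arm is illustrative only and depends on the assumed 10% to 30% share and on no conversion at all. The share affected, the net direction and the effect on the arm comparison are unknown. It is worth correcting before data collection, because missing information on form and size cannot be restored by analysis.

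**What to change.** Use one correction only.

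**Preferred.** Keep the baseline picture as the fixed reference unit in all arms. Replace the one-off wording with an instruction to convert whenever form, potency or size differs from that picture, whether occasionally or lastingly. Add a weight-conversion aid to the equal-weight page. Ask usual form and size again at 6 weeks and 3 months, as a consistency check or for a sensitivity analysis. The declared outcome, standard joints per week, is unchanged.

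**Alternative.** Record unconverted counts together with the picture current at each assessment, and derive quantity as count × weight × the 1:2:3 factor. In that case there must be no conversion in the diary as well.

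Doing both corrects twice. Take 14 joints of 1/2 g (7 g) that become 14 joints of 1/4 g (3.5 g), a true cut of 50%. Converted to the baseline picture this is 14 × (1/4)/(1/2) = 7 units. Multiplying those units by the current 1/4 g gives 1.75 g, and 1 − 1.75/7 = 75%, a false result.

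The cost is a slightly longer assessment, using pictures that are already planned, and somewhat more effort for participants when they fill in the diary. The alternative also moves the outcome from joints to potency-weighted grams that rest on a rule of thumb.

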**Figure 1 F1:**
[figure not shown]
**Trial flowchart.** This figure provides an overview of the participant flow for this trial.

Study arm one and two involve weekly reminder e-mails to login and fill out a consumption diary. The following modules, organized into three main parts, are offered as a web-based self-help intervention (study arms one and two):

• Part 1: Introduction

• Registration process

• Explanation of the cannabis consumption diary and its fully automated progress charts and statistics

• Examination of the pros and cons resulting from a change in cannabis consumption patterns and further principles of motivational interviewing to address motivation

• Explanation of the “My Can Reduce” folder (this folder allows individuals to review the acquired summarized module documents, e.g., the list of the top five strategies for dealing with cannabis cravings)

• Explanation of the emergency button for immediate responses to frequently asked questions and access to emergency contacts

• Part 2: Key Modules (participants are encouraged to complete these modules in the order presented below)

• Module 1: Strategies for goal achievement

• Module 2: Identifying risk situations

• Module 3: Dealing with cannabis craving

• Module 4: Dealing with relapses

• Part 3: Further Modules (participants are encouraged to complete at least two, in any order)

• Module 5: Tobacco smoking during the reduction of cannabis use

• Module 6: Saying “no” to foster refusal skills

• Module 7: Dealing with burdens

• Module 8: Preserving achievements

Furthermore, a glossary that explains the terms, definitions, and concepts used in the intervention, information about the history of cannabis use, the short-, medium- and long-term effects of cannabis, the physical risks of cannabis (COPD, lung cancer, cardio-vascular, etc.), co-occurring mental health problems (depression, psychosis, ADHD, etc.), and harm reduction techniques for the use of cannabis with recommendations (these recommendations favor oral intake and are based on the recommendations for medical cannabis use
[29,30]) will be provided in an appendix accessible after login, along with frequently asked questions and their corresponding answers.

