The additional two chat counseling sessions in study arm one will apply support regarding behavioral change according to MI, discuss the modules of the web-based self-help part based on MI and CBT, review the development of the consumption diary and will be structured as follows:

• Chat session 1: Starting point and objective agreement

• Personalized feedback according to baseline assessment of cannabis related physical and mental health risks

• Review of successful strategies of change related to topics other than cannabis

• Imagining daily routines after cannabis cessation; exploration of aims to live without, and the dissonances of, cannabis use; mobilization of social support with the invitation for a relevant third person to join chat session 2

• Agreeing on a cannabis use objective expressed in tangible numbers (e.g., a maximum of two standard joints per week, complete cannabis abstinence etc.)

• Chat session 2: Experience exchange and consolidation

• Experience exchange regarding the agreed-upon objective since the starting point

• Review of the patterns of the consumption diary goals and achievements

• Review and consolidation of web-based self-help modules

• Experience and improvement of social support

• Revising objectives

• Saving strategies for long-term success

The web-based self-help intervention and the subsequent tailored chat counseling aim to reduce cannabis use. However, those participants who seek cannabis abstinence will also be encouraged to make step-by-step reductions until full abstinence has been reached. The maintenance of abstinence from one day to the next, as is recommended by the content of tobacco prevention websites
[31], will not be advised for safety reasons (e.g. to avoid possible severe withdrawal symptoms).

Participants randomized to the waiting list will have the opportunity to participate in the web-based self-help intervention 3 month after registration. Follow up measures for those participants will be assessed online or by telephone interviews for those participants who cannot be reached online at the 3 month follow up.

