^1)^ Additional retrospective cost-relevant information directly or indirectly related to cannabis use will be collected by the CLAMES to conduct cost-effectiveness and cost-utility analyses.

^2)^ 7-day point prevalences of the quantity (in common standard joints) and frequency (the number of days on which cannabis is used) of cannabis use will be derived from the consumption diary assessed daily using data from the last 7 days.

Moreover, the following secondary outcome instruments will be applied: 1) cannabis consumption days per week according to the consumption diary; 2) the Cannabis Use Disorders Identification Test (CUDIT), which is a 10-item questionnaire
[33] that was constructed by adapting the Alcohol Use Disorders Identification Test (AUDIT
[34]). To cover the length of the trial length, this instrument will be adapted to focus on the last 3 months in its planned assessments (baseline and 3-month follow up); 3) The Severity of Dependence Scale (SDS), which is a 5-item questionnaire that measures the severity of cannabis dependence. Each of the five items is scored on a 4-point scale (0–3). The total score is obtained through the addition of the ratings on all 5 items. High scores indicate high levels of dependency
[35]; 4) The Cannabis Withdrawal Scale (CWS)
[36], which is a 26-item questionnaire containing statements that describe cannabis withdrawal symptoms within the last 24 hours on 11-point scales (0–10); 5) The Cannabis Craving Symptoms questionnaire (CCS-7), which is a 7-item questionnaire
[37] derived from the Marijuana Craving Questionnaire
[38]. Each item is rated on a 7-point-scale (1–7); 6) the “Fragebogen Substanzanamnese” (FDA), which is a questionnaire that ascertains the number of years of consumption over the lifetime, the past month’s consumption, and the manner of consumption for DSM-IV/ICD-10 substances of abuse. This measure was derived from the Europe ASI
[39]; 7) the short version of the Mental Health Inventory (MHI-5)

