[40], which is a validated and user-friendly self-assessment questionnaire that assesses recent mental distress and self-reported diagnoses of depression; 8) the CLAMES, which is a standardized measure of functional health states that provides a simple, generic measure of health for clinical and economic appraisal. This instrument consists of a descriptive system to measure pain/discomfort, physical functioning, emotional state, fatigue, memory and thinking, social relationships, anxiety, speech, hearing, vision, and use of hands and fingers on four or five levels that range from no problems to extreme problems
[41]. Overall intervention satisfaction will be ascertained on a visual analogue scale from absolutely unsatisfied to absolutely satisfied. Finally, retention will be derived from the last cannabis use input entered into the consumption diary in study arms one and two.

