### Trial flow

Figure 
1 provides an overview of the trial flow. If a participant successfully completes the baseline assessment (t0), he or she will be introduced step-by-step into the corresponding study arm, invited to participate in part one (study arms 1 and 2), or informed that they will be provided access to the web-based self-help within approximately 12 weeks (waiting list condition). Participant in the intervention arms 1 and 2 will receive automated e-mail notifications to login and enter their cannabis consumption frequency and quantity into their consumption diary every week. Access to all modules will be unrestricted from day one. However, the participants will be encouraged to complete all key modules (modules 1–4) in order, to complete at least two further modules chosen from modules 5 to 8 and to repeat any modules they feel they need or that they perceived as helpful within the 6 weeks of duration of study arms 1 and 2.

Six weeks after the baseline assessment, participants will again be invited by e-mail to login and complete the final study assessment (t1). Participants will be invited to complete the follow up assessment (t2) by an e-mail message that will be sent 3 months after t0; this message will inform the participants that completion of the entire 3-month follow up assessment will be compensated with 40 Euro (via an online voucher or an online charitable donation).

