### Handling of study dropouts

Each week, participants in intervention arms one and two will be sent an automated e-mail that will contain a reminder to login to their consumption diary, a reminder to work on their modules and a direct link to the Can Reduce login site. If participants do not log in, they will receive a reminder e-mail every three days for the following two weeks. If they do not continue their participation after these reminders, they will be considered to have dropped out of the study. Participants allocated to study arm 1 (chat and self-help) will additionally be invited to the first chat session at least three times over two weeks if they do not respond. In each of these invitations they will be asked to agree to attend two chat sessions on dates suggested by their counselor. If the participants are unable to attend on these dates, they will have the opportunity to suggestion dates to the counselor. This procedure will be repeated until a first chat date has been found. If participants do not show up at the agreed chat date they will be sent new chat dates until a first chat appointment occurs. If participants do not reply after three invitations to schedule chat appointment, they will be considered to have dropped out of the study. The second chat appointment will be scheduled at the end of the first chat session. If participants do not show up for the second session, they will be sent new chat dates twice. Attendance of at least one chat appointment will be required of the participants, otherwise they will be considered to have dropped out. Participants in study arm 1 who discontinue their consumption dairies but proceed with the chat session will not be considered as drop outs and will be included in the study.

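### The primary outcome is defined from a daily diary that is described only for the two active arms and cannot exist at baseline, so the contrasts with the waiting list may rest on different instruments or modes

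*Protocol article*

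**What the plan says.** All places are in the Protocol article.

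- **Outcome.** The section on aims states: "The primary outcome is the weekly quantity of cannabis consumed (measured in the number of standard joints per week) at the 3-month follow up". In the section on hypotheses it is framed as the reduction between baseline and 3 months.
- **Source of the data.** Measurement instruments, Table 1 footnote 2: 7-day quantity and frequency "will be derived from the consumption diary assessed daily using data from the last 7 days". Table 1 marks both at baseline, weeks 1, 3 and 6, and 3 months. Neither the table nor the footnote makes an exception by arm or visit.
- **Who keeps the diary.** Study interventions: "Study arm one and two involve weekly reminder e-mails to login and fill out a consumption diary". Trial flow: participants in arms 1 and 2 are prompted by e-mail to "enter their cannabis consumption frequency and quantity into their consumption diary every week". Handling of study dropouts sends the diary reminder to the same two arms: "Each week, participants in intervention arms one and two will be sent an automated e-mail that will contain a reminder to login to their consumption". Measurement instruments: "retention will be derived from the last cannabis use input entered into the consumption diary in study arms one and two".
- **What the diary is.** It is introduced in Part 1 of the self-help programme, with automated progress charts. The Discussion treats it as part of that programme: "During the online implementation of the consumption diary of the web-based self-help intervention".
- **Waiting list.** Access to the self-help comes after about 12 weeks (Trial flow) or 3 months (Study interventions). On its follow-up, Study interventions says: "Follow up measures for those participants will be assessed online or by telephone interviews for those participants who cannot be reached online".

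**The concern.** Hypotheses 1 and 2 compare arms 1 and 2 with the waiting list on change in weekly joints. If the 3-month value comes from a running diary in the active arms and from a single questionnaire or interview in the waiting list, any systematic difference between those methods is counted as treatment effect. Randomisation does not protect against this, because the difference arises after allocation. The diary is also a treatment component, with charts and consumption goals, so using it may itself change what is reported.

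The second issue is missing data. If only diary entries count, whether an active-arm participant has a primary outcome depends on adherence to the programme. The waiting list has no such link, and the planned imputation draws on baseline variables, which do not record adherence.

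**Working it through.** The point itself has no arithmetic. It rests on comparing the sections.

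**Baseline.** The baseline assessment is completed before randomisation, and participants are led into their arm, where the diary is explained, only afterwards (Baseline assessment; Randomization and allocation; Trial flow). A daily diary of the preceding 7 days cannot exist then. Taken literally, footnote 2 fails at baseline in all three arms.

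**3 months, arms 1 and 2.** The intervention lasts 6 weeks. A diary-based value at 3 months needs daily entries to continue for roughly six more weeks. The dropout section keeps in the study arm 1 participants who stop the diary but go on with the chat. Under footnote 2 as written, no source for their quantity is named.

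**3 months, waiting list.** No section gives this arm a diary before the 3-month assessment. Its follow-up is online, or by telephone for those not reached online. The quantity measure asks participants to match their use to photographs, which a telephone interview cannot show in the same way. No telephone route is described for arms 1 and 2.

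**Fallback outcome.** Because the joint measure is new to trials, the Discussion says use days will also be relied on. Footnote 2 takes use days from the same diary, so they offer no independent check.

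**Scale of the planned effect.** The documents give no figure for a diary-versus-recall difference. What can be shown is how small the planned effect is. The plan states Cohen's f = 0.15, 89 per arm, 80% power and α = 5%.

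- The stated 89 reproduces for a repeated-measures F-test with 2 groups and 2 times if the correlation is taken as 0, which the article does not state. With N = 178, λ = N·f²·2/(1 − 0) = 178 × 0.0225 × 2 = 8.01, and power is 0.804. A one-way two-group F-test would need 176 per arm.
- Purely for illustration, assume a shift of 0.15 SD at 3 months in one arm only. If f describes a single two-group comparison, the planned difference is 2 × 0.15 = 0.30 SD and the shift is 0.15/0.30 = one half.
- If f describes the group-by-time interaction, the planned difference in change is 4 × 0.15 = 0.60 SD and the shift is 0.15/0.60 = one quarter.
- If f describes the group difference averaged over both times, the planned difference is 0.30 SD, but a shift at one of two times enters at 0.15/2 = 0.075 SD. That is again one quarter.

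The article does not say which reading was used, and the 0.15 SD is an assumption without a source.

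**The case against.** The strongest reply is that nowhere does the article say the arms are measured differently at 3 months. Table 1 is one schedule for everyone, and the e-mail invitation to the 3-month assessment is not arm-specific. Since footnote 2 also covers baseline, it may simply mean a diary-format 7-day entry built into each assessment, identical in all arms. The diary would then supply the unit of measurement and not the data stream. Form content is something a condensed article may leave to the full protocol. Much of this stands. The reference to daily assessment fits this reading poorly, but the reading cannot be excluded.

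Three stronger inferences are therefore not supported:

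- **That instrument is fully confounded with arm.** A separate instrument for the waiting list is inferred, not stated. Online is its first mode, and only those not reached online are telephoned. Weekly prompting suggests that diary entries may be partly retrospective too.
- **That a participant who completes the 3-month assessment without diary entries has no primary outcome.** Quantity is a listed item of that assessment, completion is invited and compensated separately from diary use, and missing values are to be imputed.
- **That the bias is half the planned effect.** That fraction depends on an invented shift and on one reading of f.

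The reply does not remove the conflict between footnote 2 and the sections that assign the diary to arms 1 and 2, nor the telephone route described for one arm only.

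**Conclusion.** The point holds as an inconsistency in how the primary outcome is measured, not as a demonstrated bias. The stated source cannot work at baseline for anyone and, on the procedures described, is not available in the waiting list before 3 months. The contrasts in hypotheses 1 and 2 may therefore mix treatment with instrument or mode, and active-arm participants who stop the diary may lack a diary-based value.

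Neither the size nor the direction of any bias can be derived from the document. The Discussion expects less concealment in the intervention arms. That remark is set against face-to-face therapy, so it makes differential reporting plausible but does not measure it.

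The conclusion assumes that the procedures are as the article describes them. If the full protocol already uses one form in all arms, only the wording and the telephone fallback need attention. It is still worth settling before data collection, because no analysis can restore comparable measurements that were never taken.

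**What to change.** Reconcile Table 1 footnote 2 with Study interventions and Trial flow:

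1. At baseline and 3 months, take 7-day quantity and frequency in all three arms from one identical 7-day form with the same joint pictures, placed inside the assessment.
2. Keep the running diary as process data and for the visits at weeks 1, 3 and 6. Those values support comparisons with the waiting list only if that arm completes an equivalent entry.
3. Offer the same telephone fallback, under the same conditions, to all arms, and record the mode for each participant.
4. Repeat the primary analysis in online responders as a sensitivity analysis. It selects on response, so it supports the main analysis and does not replace it.

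The cost is a few minutes of participant time at two assessments already planned, and some extra calls to arms 1 and 2.
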